### Randomization

The sample will be randomly allocated into three groups: functional circuit training group (FTG), conventional training group (CTG), and usual care group (UCG). The randomized allocation sequence will be performed by a researcher who will not be involved in the recruitment, evaluation, or training of patients, and an online platform (www.sealedenvelope.com) and concealed brown envelopes will be used. The randomization process will be carried out in blocks defined *a priori*. Evaluators will be blind as to the allocation of participants to interventions. The training will be supervised by trained physiotherapists not involved in the randomization process or evaluations.

## Procedures

### Interventions

The physical exercise program will take place over 8 weeks with a frequency of three weekly sessions of about 60 min each, totaling 24 training sessions. The sessions will begin with dynamic general stretching, after which the aerobic training will be carried out on a treadmill with a duration of 30 min, followed by the resistance training of upper limbs and lower limbs. These dynamics will occur for both the FTG and CTG, except for the third weekly session in which the FTG will perform functional training in circuit format. At the beginning, during, and at the end of the sessions, vital signs will be checked. The UCG will perform only usual care involving respiratory physiotherapy sessions that include inhalation therapy, pulmonary deflation techniques, diaphragmatic awareness, and inspiratory muscle exercise.

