Sewell et al. [28] demonstrated improvement in PADL and ADL performance after a short-term training program combining functional exercises with aerobic and home training in patients with COPD. Despite the benefits obtained, the authors did not evaluate whether the responses were maintained for a longer period of time than the program period and did not include the progressive resistance training, an essential component for these patients. It is still unknown whether the addition of a functional circuit training (structured on the basis of the limitations during ADLs) to a conventional combined aerobic and resistance training program, commonly performed and well established in PR programs, can improve PADL, ADL performance, and functionality of patients with COPD in the short term. In addition, it is unknown whether possible functional and PADL gains obtained in this type of training are maintained during a 3-month follow-up.

This randomized clinical superiority trial aims to evaluate the effects of the addition of a circuit of functional physical training to an 8-week combined training (aerobic and resistance) on PADL, ADL performance, functional exercise capacity, and peripheral muscle strength of patients with COPD. In addition, the effects of the interventions will be re-evaluated 3 months after the training completion. It is hypothesized that the proposed functional training will lead to behavioral changes, influencing the improvement in the performance of ADLs and, consequently, PADL, accompanied by functional improvement in patients with COPD.

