#### Functional circuit training

In order to maintain the same increment dynamics of resistance training in both training groups (FTG and CTG), the session that will include circuit format functional training in the FTG will be divided into two stages: functional circuit and resistance training (elbow flexion, knee extension, and flexion). The circuit training will be composed of 12 exercises (stations) that will simulate ADLs, elaborated on the basis of previous identification (telephone interview) of the main limitations for performing ADLs, reported by patients with COPD from the database of the care center where the study will be conducted.

Each exercise will last 2 min and 30 s, so the total duration of the functional circuit will be 30 min, as performed in aerobic training. Following the same method of aerobic training, the increment in the training intensity will be performed on the basis of the subjective sensation of dyspnea of the individuals, measured using the Borg scale [38, 41]. Thus, when the individual reports a dyspnea sensation with values between 4 and 6 on the Borg scale, the intensity will be maintained, this being considered an adequate training intensity [38, 41]; however, when the intensity is less than 4, the training intensity will be increased (that is, an increase in the speed/number of repetitions of the exercises until the 8 weeks of training is completed). A pilot session was conducted with patients with COPD to evaluate the viability and execution time of functional training in circuit format. There were no problems in the execution and time of the exercises and these were shown to be feasible by the patients.

The functional circuit will include the exercises/stations described below and illustrated in Fig. 2:

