## Discussion

### Potential impact and significance of the study

The present proposal was developed through extensive literature research on this topic. Through the interpretation of the results found in several studies, it was possible to develop this concise and structured training protocol. The use of this protocol in the treatment of COPD will confirm whether the addition of functional physical training to a conventional training will promote positive effects on PADL and functionality and whether there will be maintenance of possible gains at the 3-month post-training follow-up.

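### The aim and planned conclusion speak of adding a functional circuit to conventional training, but the schedule puts it in place of one third of the treadmill sessions

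*Protocol article*

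**What the plan says.** **Aim and conclusion.** The Introduction says the trial will "evaluate the effects of the addition of a circuit of functional physical training to an 8-week combined training (aerobic and resistance"). Under Potential impact and significance of the study, use of the protocol "will confirm whether the addition of functional physical training to a conventional training will promote positive effects on PADL and functionality".

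**Schedule.** Interventions gives both training groups "three weekly sessions of about 60 min each, totaling 24 training sessions". In these, "the aerobic training will be carried out on a treadmill with a duration of 30 min", followed by resistance work. The two groups follow the same pattern "except for the third weekly session in which the FTG will perform functional training in circuit format".

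**Content of the circuit session.** Functional circuit training says that this session "will be divided into two stages: functional circuit and resistance training (elbow flexion, knee extension, and flexion"). It has twelve stations of 2 min 30 s each, "so the total duration of the functional circuit will be 30 min, as performed in aerobic training". The Study design section agrees: a conventional session is resistance plus aerobic work, and a circuit session is resistance plus circuit.

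**Outcomes.** The primary outcome is accelerometer-measured physical activity in daily life. Limitation in daily activities, the 6-minute walk test (6MWT) and peripheral muscle strength are secondary.

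**The concern.** An add-on question compares conventional training plus a circuit with conventional training alone. Here the resistance component is deliberately kept the same in both groups, and the treadmill block gives way to the circuit. No arm receives the full conventional programme and the circuit as well.

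What is at stake is the claim made from the result. If FTG and CTG do not differ, the planned wording would lead to the conclusion that adding functional training does not help, although a gain from the circuit might have been offset by less treadmill work. The article also looks ahead to inserting such a circuit into rehabilitation programmes (Contribution and clinical applicability). A centre acting on the result needs to know whether the circuit was tested on top of aerobic sessions or in place of some of them.

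**Working it through.** **1. The article's own figures.** Interventions: 3 sessions/week × 8 weeks = 24 sessions, as stated. Functional circuit training: 12 stations × 2.5 min = 30 min, as stated.

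**2. Volume by group.** The inputs are 30 min of treadmill per conventional session and one weekly FTG session with the circuit in place of the treadmill.

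| | FTG | CTG |
|---|---|---|
| Treadmill sessions | 2 × 8 = 16 | 3 × 8 = 24 |
| Treadmill minutes | 16 × 30 = 480 | 24 × 30 = 720 |
| Circuit sessions | 1 × 8 = 8 | 0 |
| Circuit minutes | 8 × 30 = 240 | 0 |
| Treadmill plus circuit | 720 | 720 |
| Resistance sessions | 24 | 24 |

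The FTG has 24 − 16 = 8 fewer treadmill sessions, which is 8/24 = one third, or 240 min. An add-on arm would have had 720 + 240 = 960 min.

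**3. What the contrast estimates.** For illustration, assume that effects simply add up. Let t be the effect of one treadmill block, c that of one circuit block, and R that of the 24 resistance sessions.

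- CTG: R + 24t
- FTG: R + 16t + 8c
- Full conventional training plus circuit (no such arm): R + 24t + 8c
- FTG − CTG = 8c − 8t
- Add-on effect = 8c

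The two differ by 8t, and comparing FTG with CTG cannot separate c from t.

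- If t > 0, FTG − CTG is smaller than the add-on effect. A null difference could then mean either c = 0 with a small t, or a positive c offset by t. A positive difference would imply a positive add-on effect.
- If t = 0, the two coincide.
- If t < 0, a positive FTG − CTG need not imply any add-on benefit.

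**4. Walking as opposed to treadmill time.** Stations 8 (steps and ramp), 9 (rising and walking 3 m) and 11 (walking among hoops) involve gait or steps: at most 3 × 2.5 = 7.5 min per circuit, or 7.5 × 8 = 60 min over the programme. Counted in full, they bring the FTG to at most 480 + 60 = 540 min against 720 min. That is 180/720 = 25% less. The shortfall is thus one third in treadmill time and between 25% and 33% in treadmill plus gait-station time.

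**The case against.** The strongest reply is that this is a matter of wording. The swap is openly described in three sections, and the Abstract's talk of a combination, with its three-component label for the first group, fits the schedule. Addition can be read as bringing a third modality into a two-modality programme. Matching time is also defensible, because a true add-on arm would mix circuit content with extra exercise time. All of this stands, except that the loose reading strains against the planned conclusion, where the circuit is added to a conventional training that the FTG does not receive in full.

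A reader might infer three stronger things that the documents do not support:

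- **That the design or the randomised comparison is flawed.** It is not. FTG versus CTG validly answers a replacement question.
- **That a positive result would say nothing about adding the circuit.** If treadmill work is neutral or beneficial, an FTG advantage obtained with less of it is indirect and probably conservative support for adding the circuit.
- **That offsetting threatens every outcome equally.** Sample size calculation assumes that steps will not rise in the CTG, which receives the full treadmill volume. If neither conventional component lowers steps, that premise puts t at about zero, and the replacement and add-on effects on steps nearly coincide. This is a planning assumption and not evidence, but it weakens the argument for the primary outcome. The argument applies mainly to the 6MWT and the other secondary outcomes.

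For the 6MWT, the one-third figure is treadmill time and not all walking. The circuit is also progressed to the same dyspnoea range as the treadmill, so a fall in overall training effort cannot be read from it.

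**Conclusion.** The point holds as a mismatch between the stated objective and the contrast the arms provide. The aim and planned conclusion are worded as an add-on effect. The schedule delivers replacement of 8 of 24 treadmill blocks (240 of 720 min) by circuits, with total time and resistance sessions equal. These counts assume that sessions are delivered as the article describes.

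A positive FTG–CTG difference would support replacement directly, and adding the circuit only on the untested assumption that treadmill work is not harmful. A null or negative difference would not show that adding a circuit is useless. The ambiguity matters most for the 6MWT and the other secondary outcomes. The wording should be corrected because it changes what the trial can claim, but the randomised comparison and the sample size are unaffected.

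**What to change.** Reconcile the aim in the Introduction and the claim under Potential impact and significance of the study with Study design, Interventions and Functional circuit training. If sessions are delivered as those three sections describe, word the objective, hypothesis and conclusion as the effect of replacing the treadmill block in one of three weekly sessions with a functional circuit, at equal total time and equal resistance sessions.

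The cost is a few sentences. Conduct, data collection and sample size do not change. This takes no view on which schedule is right.

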#### Resistance training

For the training prescription, a 1-repetition maximum (1RM) test will be performed, according to a previously described protocol [36, 37], of the following muscle groups: elbow flexors and knee extensors and flexors. The resistance training will be performed using weight machines: extensor chair and flexor chair (Ipiranga® - Brazil) for lower limbs and simple pulley equipment (Ipiranga® - Brazil) for upper limbs. The intensity of training will follow the protocol recommended for patients with COPD [38, 39], 60 to 80% of the 1RM test, with three sets of 10 repetitions, and 2-min intervals between sets. The load increase will be performed every four stimuli (sessions) with a 5% increase in the intensity of the 1RM test until reaching 80%. The trained muscle groups will be the same as previously described in the 1RM test.

#### Aerobic training

The aerobic training will be performed on an ergometric treadmill and will begin with an intensity of 80% of the average speed reached in the 6MWT [40]. In addition, the increase in aerobic training intensity will be performed on the basis of the subjective sensation of dyspnea of the individuals, measured by the Borg scale [38]. Thus, when the individual reports a dyspnea sensation with values between 4 and 6 on the Borg scale, the intensity will be maintained, this being considered an adequate training intensity [38, 41]; however, when the intensity is less than 4, there will be a 5% increase in training intensity.

#### Functional circuit training

In order to maintain the same increment dynamics of resistance training in both training groups (FTG and CTG), the session that will include circuit format functional training in the FTG will be divided into two stages: functional circuit and resistance training (elbow flexion, knee extension, and flexion). The circuit training will be composed of 12 exercises (stations) that will simulate ADLs, elaborated on the basis of previous identification (telephone interview) of the main limitations for performing ADLs, reported by patients with COPD from the database of the care center where the study will be conducted.

Each exercise will last 2 min and 30 s, so the total duration of the functional circuit will be 30 min, as performed in aerobic training. Following the same method of aerobic training, the increment in the training intensity will be performed on the basis of the subjective sensation of dyspnea of the individuals, measured using the Borg scale [38, 41]. Thus, when the individual reports a dyspnea sensation with values between 4 and 6 on the Borg scale, the intensity will be maintained, this being considered an adequate training intensity [38, 41]; however, when the intensity is less than 4, the training intensity will be increased (that is, an increase in the speed/number of repetitions of the exercises until the 8 weeks of training is completed). A pilot session was conducted with patients with COPD to evaluate the viability and execution time of functional training in circuit format. There were no problems in the execution and time of the exercises and these were shown to be feasible by the patients.

The functional circuit will include the exercises/stations described below and illustrated in Fig. 2:

**Fig. 2 Fig2:**
[figure not shown]
Functional circuit exercises

Exercise 1: Simulate drying the back: pass the stick behind the back (as if drying the back with a towel) and change hands every five movements.

Exercise 2: Simulate sweeping the floor: With shoulder flexion at about 75°, hold the stick with the forearm pronated and perform a movement similar to “rowing”.

Exercise 3: Simulate tying shoes: Sitting in a chair with 90° elbow flexion, hold a ball with the hands, then perform knee flexion, touching the lateral malleolus on the contralateral knee, with the ball touching the medial malleolus.

Exercise 4: Simulate passing a squeegee on the floor: Holding a stick (the stick should touch the ground) with the hands, move the stick anteriorly to the left and then to the right and then repeat on the contralateral side.

Exercise 5: Simulate bath movements to wash the hair: Holding a small ball in the hands, perform simultaneous movements: 90° shoulder flexion, 90° elbow flexion, and touch the ball on the head.

Exercise 6: Simulate picking up objects in high and low places: In front of a bookcase in the orthostatic position, pick up a ball from a high shelf (head level) and then put it on two lower shelves (chest level and waist level).

Exercise 7: Simulate squatting: Squat holding a fixed bar.

Exercise 8: Simulate walking on uneven ground using ramps and stairs: Rise and descend steps/ramp.

Exercise 9: Simulate standing up and sitting in a chair: Get up from the chair, walk a short distance (3 m), and sit in the chair again.

Exercise 10: Simulate changing clothes: With a hula hoop on the ground, step with both feet inside the circle, crouch to pick up the hula hoop with both hands, rise up holding the hula hoop, and perform shoulder flexion by lifting the hula hoop so that it runs all over the body of the individual; reverse the movement with the same steps, ending by placing it on the floor again.

Exercise 11: Simulate the avoidance of obstacles during gait: With five hula hoops on the ground, walk among the hula hoops.

Exercise 12: Simulate picking up objects: In front of three small cones on the floor, perform trunk flexion and touch the tip of one of the cones and return to the starting position and repeat the movement until having touched all the cones. When finishing the three movements, perform them with the other hand (Fig. 2).

### Participant timeline

The time schedule of enrollment, interventions, and assessments is outlined in Fig. 3. Recruitment of study participants began in July 2018.

**Fig. 3 Fig3:**
[figure not shown]
Content for the schedule of enrollment, interventions, and assessments. *Abbreviations*: *CTG* conventional training group, *FTG* functional circuit training group, *LCADL* London Chest Activity of Daily Living, *PADL* physical activity in daily life, *UCG* usual care group.

## Results

The primary outcome will be the PADL assessment using accelerometry. Secondary outcomes are limitations on performance in ADLs, functional exercise capacity, and peripheral muscle strength. The evaluations will be carried out by the same evaluators at all described moments.

### Primary outcome

The PADL will be used as the primary outcome of the study, measured by step counts days and time spent on activities, using an accelerometer-type movement sensor, ActiGraph GT3X (ActiGraph LLC, Pensacola, FL, USA), which measures and records acceleration variations with magnitudes ranging from approximately 0.05 to 2.5 G (g = 9.8 m/s [2]) within a frequency range of 0.25 to 2.5 Hz. Each sample of counts will be summarized over a specific time interval of 60 s, called an epoch. Accelerometers will be placed on the waist immediately below the umbilical scar, and individuals will wear the equipment for 7 days. The accelerometer will be removed during the nighttime sleep period and when the participant has contact with water (personal hygiene or water activities). Participants will wear the device before and after the intervention periods and soon after the 3-month post-intervention follow-up. For analysis of the data, specific *software* will be used (ActiLife5 – Data Analysis Software by ActiGraph).

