**Methods:**

In this randomized controlled trial, patients with COPD will be randomly assigned (1:1:1) to an 8-week training program to follow one of the three *a priori* defined groups: (I) resistance and aerobic and functional exercises, (II) a conventional program including only resistance and aerobic exercises, or (III) a usual care program. Patients will be evaluated before and upon completion of 8 weeks of training regarding physical activity in daily life (PADL) using an activity monitor (accelerometer), activities of daily living (London Chest Activity of Daily Living), functional exercise capacity (6-minute walk test), and muscle strength (dynamometry). Additionally, the sustained effects of the interventions will be evaluated 22 weeks after commencing the study.

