### Sample size calculation

This is a superiority trial in which sample size determination was performed through prior study [45] information based on the primary PADL variable. With the expectation of an increase in the number of steps of 45% (approximately 2260 steps) in the FTG compared with the CTG and UTG (both with no expected increase), using a standard deviation of 2603 steps, and loss at follow-up of 20% of individuals (values commonly found in the study population) [44], 25 individuals will be required in each of the three groups to obtain a power of 80%, adopting an α of 5%.

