### Statistical analysis

The statistical program SPSS 22.0 (IBM, Armonk, NY, USA) will be used. The data will be submitted to the normality test of Kolmogorov–Smirnov, and if they present normal distribution, the descriptive variables will be expressed as mean and standard deviation; if they do not fit the Gaussian distribution model, data will be presented as median and interquartile range. Mauchly’s sphericity test will be performed. Once the sphericity is assumed, two-way analysis of variance (ANOVA) will be performed to evaluate the possible intra- and inter-group differences (FTG, CTG, and UCG) at pre-intervention, post-intervention, and post-*follow-up*. The Tukey post-hoc will be used to identify the specific differences in the variables in which the F values found are higher than the established statistical significance criterion. To evaluate the effect size between interventions, Cohen’s d test will be used. The level of significance adopted will be 5%. Data integrity will be monitored by regularly scrutinizing data files for omissions and errors. Participants will be given an anonymous study ID to protect confidentiality, and only study investigators will have access to the final trial data set.

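### The primary outcome is two accelerometer measures on equal terms, but the sample size rests on steps alone and no rule shares the 5% level between them

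*Protocol article*

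**What the plan says.** The opening of the Results section names only a construct: "The primary outcome will be the PADL assessment using accelerometry". The Primary outcome section then makes it concrete: "The PADL will be used as the primary outcome of the study, measured by step counts days and time spent on activities". Neither measure is placed above the other, and activity time does not appear among the secondary outcomes. On timing, the same section says: "Participants will wear the device before and after the intervention periods and soon after the 3-month post-intervention follow-up".

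The Sample size calculation is worded for one variable, with "information based on the primary PADL variable", and the figure it uses is "increase in the number of steps of 45% (approximately 2260 steps) in the FTG". No effect or SD is given for activity time.

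The Statistical analysis section plans a two-way ANOVA of the three groups over the three assessments, followed by Tukey comparisons where F is significant. On the error rate it says only "The level of significance adopted will be 5" per cent.

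The Methods part of the Abstract introduces the later assessment in these words: "Additionally, the sustained effects of the interventions will be evaluated 22 weeks after commencing the study". The Introduction likewise puts the effect over the 8-week training first and adds the 3-month re-evaluation after it.

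**The concern.** The outcome section and the sample-size section do not describe the same primary outcome. One has two measures of equal standing; the other has a single variable, steps. Tukey's procedure handles the several comparisons within one variable. It does nothing about having two variables, each of which could carry the primary claim.

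Two things are at stake. A report of a benefit on activity time alone, with no difference in steps, could be presented as a positive primary result by following the outcome section literally. The stated 5% and 80% would then describe steps alone and not the primary outcome as defined.

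**Working it through.** **Inputs.** From the Sample size calculation: difference 2260 steps, SD 2603 steps, loss 20%, alpha 5%, power 80%, 25 per group. From the Abstract: allocation 1:1:1. Assumed, because not stated: two-sided testing; one deciding F test per variable; the correlation between the two measures, taken from 0 to 0.9.

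**Step 1: the plan's own figure, for steps alone.**
- Two-group normal formula: n = 2 × (1.960 + 0.842)² × (2603/2260)² ≈ 20.8, so 21 evaluable per group. For 20% loss, 21/0.8 = 26.25, so 27; the cruder 21 × 1.2 = 25.2 gives 26. The stated 25 is within two patients.
- Three-group ANOVA with means 2260, 0, 0: f = (2260 × √2/3)/2603 = 0.409, which needs 60.6, so 61 evaluable. 61/0.8 = 76.25, so 77 in total against 75 stated.

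The sample size is thus essentially reproduced for steps. With 25 × 0.8 = 20 evaluable per group, power for steps is 79.5% (ANOVA F test), 78.4% (normal formula) or 76.3% (two-sample t test).

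**Step 2: either measure counts as success.** With two independent tests at 5%, the family-wise error is 1 − 0.95² = 9.75%. For correlated measures it was simulated in two ways: two normal test statistics (400,000 sets), and two three-group F tests with 20 per group (40,000 sets).

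| Assumed correlation | Two normal tests | Two three-group F tests |
|---|---|---|
| 0 | 9.75% (exact) | 9.8% |
| 0.5 | 9.1% | 9.2% |
| 0.7 | 8.3% | 8.5% |
| 0.9 | 7.0% | 7.0% |

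Every entry exceeds 5%.

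**Step 3: both measures must succeed.** The false-positive rate then cannot exceed 5%. Joint power cannot exceed the power of either test, so it is at most 76.3% to 79.5% at the planned loss. The protocol gives nothing from which to compute power for activity time. If it were equal to that for steps and the two tests were independent, joint power would be 0.763² = 58% to 0.795² = 63%.

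**Step 4: what the repairs cost in patients.**
- Steps as the single primary variable: alpha 5%, 25 per group, no change on this account.
- Two primary variables at 2.5% each: 26 evaluable per group by the normal formula; 26/0.8 = 32.5, so 33 per group and 99 in total. If the trial stays at 20 evaluable per group, power for steps falls from 78.4% to 69.3%.

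**The case against.** The strongest reply is that the document already points to steps: the sample-size section refers to one primary variable, and steps are the only one it uses. That stands as far as it goes. It would be too strong to say that nothing identifies steps as the deciding variable. But the section that defines the primary outcome still gives activity time the same status, so the two sections need aligning.

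A second reply is that both measures come from the same device over the same seven days and are probably well correlated, so independence is an unlikely extreme. This also stands. It moves the figure towards the 7% end without bringing it to 5%.

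A third is that an analysis plan or full protocol may settle the order of testing. That may be so, and the absence of a testing order is not itself the complaint. The complaint is that the definition printed here conflicts with the sample-size basis printed here. For the same reason, the article does not show that the choice of headline result has been left until the data are seen.

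A reader might also infer that two measures at two post-baseline times make four separate tests at 5%, with a family-wise error of roughly 11% to 18%. The document does not support that. Both times enter one ANOVA per variable, with Tukey only after a significant F, and the Abstract and Introduction present the 3-month assessment as additional. Nor does it support further inflation from splitting activity time into intensity bands, since it mentions none.

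**Conclusion.** The point holds in a limited form. The primary outcome is defined by two measures of equal standing, while the sample size is built on one of them, and nothing stated links the two at the 5% level. Under an either-measure rule the family-wise error is about 7% to 10% instead of 5%. Under a both-measures rule alpha holds, but joint power is below the stated 80% at the planned 20% loss. The protocol states neither rule, so each figure is conditional on one of them, and the first also on assumed correlations. The mismatch between sections is certain; the exact error rate is not. The sample size is not wrong for steps alone, and the trial is not invalidated. The definition should be settled before the data are analysed.

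**What to change.** In the Primary outcome section, name mean steps per day as the single primary variable, as the Sample size calculation implies, and the end of the 8-week training as the primary time, as the Abstract and Introduction imply. List activity time and the 3-month follow-up as secondary, and carry the same wording into the Statistical analysis section so that it is clear which comparison carries the primary claim.

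Keep the three-group comparison with Tukey. The sample-size section compares the functional circuit group with both other groups, so restricting the primary contrast to the conventional training group would not follow from it and is not needed for this repair.

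The cost is a few sentences and the primary status of activity time. The 75 patients need no change on this account. If the investigators prefer to keep both measures as primary, they should state the success rule and accept either the larger trial or the lower power worked out above.
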